### 2.2 Sample selection

To meet this study’s purpose and ensure the study subject’s safety, patients who meet the following inclusion criteria and do not violate the exclusion criteria will be eligible.

#### 2.2.1 Inclusion criteria

Outpatients who meet all of the following criteria will be eligible:1. Patients with T2D treated with diet and exercise alone, diet and exercise plus α-GI (excluding acarbose) or metformin, or both drugs in combination2. Male or menopausal female patients aged ≥20 years on the day of consent3. Patients with an HbA1c of >6.5% and ≤8.5% on the date of consent4. Patients with a stable dosage of their diabetes medications from 4 weeks before the day of consent until the day of consent5. Patients who have provided written informed consent to participate in this study

#### 2.2.2 Exclusion criteria

Patients who fall into any of the following exclusion criteria on the day of consent will be excluded:1. Patients taking diabetes medications other than α-GI and metformin2. Patients with anemia (male, <13 g/dL; female <12 g/dL)3. Patients with hypoalbuminemia (<3.0 mg/dL)4. Patients with thyroid impairment5. Patients with liver cirrhosis6. Patients with nephrotic syndrome or moderate or severe renal impairment (eGFR of <45 mL/min/1.73 m^2^)7. Patients receiving antiplatelet or antithrombotic drugs8. Patients diagnosed with malignant tumors9. Patients requiring a legal representative10. Patients with a history of hypersensitivity to any ingredients of imeglimin11. Patients with contraindications to imeglimin12. Patients with other conditions who are judged by the investigator to be inappropriate for this study

After selecting the potential study participants, the principal investigator or sub-investigators will explain the details of the study using a consent and explanation documents approved by an accredited the Certified Clinical Research Review Board (CRB) of Toho University and obtain their written consent. The principal investigator or sub-investigators will also explain that consent is given freely by the study participant and that the subject will not be unfavorably treated even if he/she does not consent, the participant may withdraw consent at any time after consent is given if he/she changes his/her mind, and that the subject will not be unfavorably treated in such cases. In addition, patients will be withdrawn from the trial if any of the following criteria apply: 1) withdrawal of consent, 2) principal investigator’s decision, based on the patient’s condition, 3) discontinuation of the study or 4) principal investigator’s decision, based on another reason. At the time of discontinuation, confirm the availability of data until discontinuation to the study subjects.

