In phase 3 clinical trials (TIMES 1–3) in Japanese patients with T2D, imeglimin, both as a single agent and in combination with other antidiabetic drugs, caused a slow decline in HbA1c that plateaued around 24 weeks after administration (Dubourg et al., 2021; Dubourg et al., 2022; Reilhac et al., 2022). In a retrospective observational study, we reported a slower decrease in HbA1c compared to glycoalbumin (GA) and a divergence in the change rate between the two when imeglimin was administered to patients with T2D (Osonoi et al., 2022a; Osonoi et al., 2022b). HbA1c levels reflect average blood glucose levels over the past 6–12 weeks, which is an indicator of long-term glycemic control, given that the erythrocyte lifespan is approximately 120 days. However, GA, a glycoprotein, is an indicator of short-term glycemic control because the half-life of albumin is shorter than that of erythrocytes at approximately 17–23 days (Takahashi et al., 2007). Therefore, GA accurately indicates changes in blood glucose levels within 2–3 weeks. However, when improvements in blood glucose levels occur in a short period of time, such as with antidiabetic drug treatment, changes in HbA1c are delayed, resulting in a transient divergence between the two. Comparing the rate of decrease from baseline in HbA1c and GA when dipeptidyl peptidase-4 (DPP-4) inhibitors are prescribed, a divergence is seen after 2 months, but thereafter, the two show almost identical trends (Shimizu et al., 2022). However, the divergence between HbA1c and GA observed with imeglimin treatment differed from the results of that report in both magnitude and duration, and short-term changes in blood glucose levels alone cannot explain this (Osonoi et al., 2022a; Osonoi et al., 2022b; Shimizu et al., 2022).

In general, factors that cause abnormal HbA1c values in the divergence between HbA1c and GA include shortening/lengthening of the erythrocyte lifespan (Panzer et al., 1982) and increased/decreased erythrocyte production (Waters et al., 1988). One of the reasons for the higher HbA1c with imeglimin treatment compared to GA may be the prolonged erythrocyte lifespan. However, erythrocyte lifespan testing is not performed in routine clinical practice.

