#### 2.3.2 Secondary outcomes

Items 1–4 below will be compared between baseline (month 0) and each time point in the pre-observation, observation, and follow-up periods, and between 6 months after imeglimin administration and each time point in the follow-up period. The change from baseline (maximum and mean values) in the pre-observation and observation periods will also be evaluated.1. Erythrocyte lifespan

Erythrocyte lifespan is calculated by measuring the carbon monoxide (CO) concentration in exhaled breath using a Carbolizer (Taiyo Co., Ltd., Osaka, Japan) and using the Strocchi et al., formula shown below (Strocchi et al., 1992):

Erythrocyte lifespan (days) = K × hemoglobin (g/mL)/endogenous CO (ppm).

K = 1380 (conversion factor).2. Erythrocyte deformability

Erythrocyte deformability is measured using a blood fluidity measuring device MC-FAN (Optima Inc., Tokyo, Japan). The microchannel array passage time of 100 μL heparinized whole blood is an index for blood fluidity.3. Red blood cell count, white blood cell count, hemoglobin concentration, and hematocrit (Ht)4. Corpuscular constant (mean corpuscular volume: MCV, mean corpuscular hemoglobin concentration: MCHC, mean corpuscular hemoglobin content: MCH)

Items 5 and 6 below will be compared between baseline and the pre-observation or observation periods.5. Measured values of HbA1c, GA, and 1,5-AG, change from baseline, and percent reduction in blood glucose with baseline as 100% (percent reduction in blood glucose will also be compared between each index at each time point)6. GA/HbA1c and 1,5-AG/HbA1c ratios

For items 7 and 8 below, data measured by the FGM system using FreeStyle Libre Pro (Abbott Diabetes Care Inc., Alameda, CA, United States of America) will be used to compare baseline with each time point during the observation period (up to 3 months after imeglimin administration). FreeStyle Libre Pro should be used following the package insert.7. Change in mean daily glucose levels and percentage decrease in blood glucose (baseline is the day before imeglimin administration)8. Mean 14-day glucose levels, estimated HbA1c levels, glucose management indicator (GMI), and respective percentage decreases in glycemia (baseline is 14 days before imeglimin administration):

Estimated HbA1c (%) = (mean glucose [mmol/L] + 2.59)/1.59.

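### The hypoalbuminaemia exclusion is printed in mg/dL, so the stated albumin cut-off cannot operate as written; most likely a unit error

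*Protocol article*

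**What the plan says.** Section 2.2.2 of the protocol article opens its list with the rule "Patients who fall into any of the following exclusion criteria on the day of consent will be excluded". Item 3 of that list is "Patients with hypoalbuminemia (<3.0 mg/dL". The item directly above it sets the haemoglobin limits in a different unit: "Patients with anemia (male, <13 g/dL; female <12 g/dL". The article states no other albumin threshold or albumin unit.

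Three other items could remove some patients with low albumin: item 5, "Patients with liver cirrhosis"; item 6, "Patients with nephrotic syndrome or moderate or severe renal impairment"; and item 12, "Patients with other conditions who are judged by the investigator to be inappropriate for this study".

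Albumin matters here because of GA. The Introduction explains the short time window of GA by noting that "the half-life of albumin is shorter than that of erythrocytes at approximately 17–23 days", and it names the divergence of HbA1c from GA and 1,5-AG as what the study sets out to confirm. Section 2.3.2 lists as secondary item 5 "Measured values of HbA1c, GA, and 1,5-AG, change from baseline", and as item 6 the ratios of GA and of 1,5-AG to HbA1c. The primary outcome in section 2.3.1 is the change in haemoglobin from month 0 to month 6. Section 2.8 makes the FAS the primary analysis population and restricts it to eligible patients who meet conditions on dosing and haemoglobin measurement.

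**The concern.** An eligibility criterion with a numeric limit should separate patients who may enter from those who may not. A limit of 3.0 mg/dL appears to lie far below any albumin concentration a patient could have, so the number separates nobody.

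Two things depend on it. First, item 3 is the only criterion set on albumin itself, in a study that compares HbA1c with a glycated-albumin marker. Section 2.2 says the criteria serve the purpose of the study as well as safety. Secondly, section 2.8 uses eligibility to define the FAS. A patient with an albumin of, say, 2.5 g/dL is eligible under the printed text and ineligible if the unit is g/dL, so two analysts could build different analysis sets from the same data.

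**Working it through.** **The figure in dispute.** The cut-off of 3.0 mg/dL is stated, not derived, so there is no calculation of the plan's to reproduce for it.

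**Inputs.**
- Cut-off: 3.0 mg/dL (section 2.2.2, item 3).
- Conversion: 1 g/dL = 1000 mg/dL.
- Serum albumin: not given in the article. Assumption: of the order of grams per dL, checked from 1.0 to 5.0 g/dL.

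**Step 1: convert the cut-off.** 3.0 mg/dL ÷ 1000 = 0.003 g/dL.

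**Step 2: compare with the assumed range.** Ratio = albumin in g/dL × 1000 ÷ 3.0.

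| Albumin (g/dL) | In mg/dL | Ratio to printed cut-off | Excluded as printed | Excluded if unit is g/dL |
|---|---|---|---|---|
| 1.0 | 1000 | 333 | no | yes |
| 2.0 | 2000 | 667 | no | yes |
| 2.9 | 2900 | 967 | no | yes |
| 3.0 | 3000 | 1000 | no | no |
| 4.0 | 4000 | 1333 | no | no |
| 5.0 | 5000 | 1667 | no | no |

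No value in the range falls below the printed cut-off. With g/dL as the unit, the cut-off is 3000 mg/dL, exactly 1000 times the printed one, and it divides the range at 3.0 g/dL. The finding is insensitive to the assumed range.

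**Step 3: is it a text-extraction fault?** Probably not. The neighbouring haemoglobin item shows its g/dL intact.

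**Step 4: does it reach the sample size?** Section 2.6 uses a haemoglobin change of −0.7 g/dL, an SD of 1.0 g/dL, two-sided α of 0.05 and 90% power, and states 24 patients. For a one-sample t-test with noncentrality 0.7 × √n, power is 0.894 at n = 23 and 0.907 at n = 24. The stated 24 is reproduced, and 30 enrolled allows for 1 − 24/30 = 20% dropout. Albumin does not enter.

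**Step 5: which outcomes depend on albumin?** The GA part of secondary item 5 and the GA/HbA1c ratio in item 6 are exposed. Haemoglobin change is measured without reference to albumin. The primary analysis is touched only through FAS membership.

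**The case against.** The strongest reply is that nobody would apply the number literally. Item 3 names a condition, hypoalbuminaemia, and the bracket only qualifies it. Investigators at this single centre would see that 3.0 mg/dL is impossible and, if their laboratory reports in g/dL, would probably apply 3.0 to that value. The error may also exist only in the article, since the board-approved protocol is not shown. This stands, and it limits the point to what the text says. It does not make the printed threshold correct, and probable site practice is something to confirm.

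A reader might go further and infer that patients with unreliable GA have been let in and that one or two of them would shift the GA mean. The article does not support that:
- Items 5, 6 and 12 remove some low-albumin patients regardless of item 3. How many would remain among these outpatients cannot be estimated and may be none.
- The article ties GA to albumin half-life but does not say that low albumin makes GA unreliable.
- It gives no GA standard deviation, no size of albumin effect and no prevalence, so a shift in the mean cannot be computed.
- The GA comparisons are largely within patient. A stable disturbance would partly cancel, although a changing one would not.

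A reader might also conclude that any low-albumin patient should be dropped from the FAS. That would take the patient out of a haemoglobin analysis that does not use albumin, on a threshold the printed text did not set.

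**Conclusion.** The point holds as an error in a stated eligibility threshold. The cut-off is 0.003 g/dL as printed and excludes no one for any albumin from 1.0 to 5.0 g/dL. The most likely cause is mg/dL for g/dL, in which case the printed value is too low by a factor of 1000. The conclusion rests on one assumption from outside the article, that serum albumin is measured in grams per dL.

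The exposure is limited to the GA-based secondary outcomes and to the meaning of eligible in the FAS definition. The sample size and the measurement of the primary outcome are unaffected. The effect on GA results is unknown and may be nil. It is worth correcting because it is a decision rule in the methods and nothing else in the article corrects it.

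**What to change.** 1. Compare item 3 with the board-approved protocol and the screening form, and correct the unit wherever it is wrong. If the error is confined to the article, correcting the article is enough.
2. Confirm which threshold was applied to enrolled patients, using the earliest available pre-treatment albumin value. The criteria apply on the day of consent, but Table 1 schedules blood tests only from month −2, so a consent-day value may not exist for everyone.
3. If any enrolled patient is below the confirmed threshold, record an eligibility deviation, settle FAS membership before database lock, and report the GA-based outcomes with and without that patient. Do not remove the patient automatically from the primary haemoglobin analysis.

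The cost is a one-line correction and a check of one laboratory value in about 30 patients. The sample size and visit schedule stay as they are.

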### 2.3 Outcome assessment

#### 2.3.1 Primary outcome

Change in hemoglobin concentration between baseline (month 0) and 6 months after treatment with imeglimin.

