## Abstract

**Background:** Imeglimin is a novel type 2 diabetes (T2D) drug that is expected to improve mitochondrial function. In its phase 3 clinical trials in Japanese patients with T2D, the hemoglobin A1c (HbA1c) decrease following imeglimin administration was slow, reaching a plateau after 20–24 weeks of treatment. In general, the erythrocyte lifespan may be a factor when HbA1c shows an abnormal value. Therefore, this study will comparatively evaluate HbA1c and other markers of glycemic control in patients with T2D after imeglimin administration and also examine the effects of imeglimin on erythrocytes.

**Methods:** This single-arm, open-label, prospective, exploratory study is designed to evaluate the divergence between HbA1c and glycoalbumin (GA) or 1,5-anhydroglucitol (1,5-AG) and the glycemic reduction rate in 30 patients with T2D with inadequate glycemic control when imeglimin 2,000 mg is administered for 6 months. In addition, we will examine the effect on erythrocytes, the presumed cause of this divergence. We will measure sustained glycemic variability using flash glucose monitoring and examine the relationship between changes in these indices and HbA1c. Moreover, because prolonged erythrocyte lifespan is a possible cause of falsely high HbA1c levels, erythrocyte lifespan, erythrocyte deformability, and hemoglobin concentration will be evaluated as effects of imeglimin on erythrocytes. Furthermore, if imeglimin has an ameliorative effect on erythrocyte deformability, it may improve peripheral arterial disease; thus, we will also evaluate the toe-brachial pressure index, a measure of this effect.

**Discussion:** In this study, if imeglimin administration results in diverging rates of hypoglycemic effect between HbA1c and GA or 1,5-AG and prolongs erythrocyte lifespan, GA and 1,5-AG, rather than HbA1c, will be considered appropriate measures of the hypoglycemic effect in the early stages of imeglimin administration. If imeglimin improves erythrocyte deformability, it may also be a new treatment strategy for peripheral arterial disease, a chronic complication of T2D.

**Ethics and dissemination:** The study protocol was scientifically and ethically reviewed and approved by the Certified Clinical Research Review Board of Toho University (approval number: THU22002). The study protocol was registered in the Japan Registry of Clinical Trials (jRCT) in December 2022 (jRCTs031220489).

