Prolonging the erythrocyte lifespan with imeglimin administration would result in a relatively high HbA1c and a slower rate of glycemic reduction than with GA or 1,5-anhydroglucitol (1,5-AG), suggesting that evaluating the glucose-lowering effect of imeglimin using HbA1c underestimates its effectiveness. There have been no reports, other than ours, on the divergence between HbA1c and GA or 1,5-AG on the glucose-lowering effect of imeglimin in patients with T2D under clinical conditions, or on its effect on erythrocytes (Osonoi et al., 2022a; Osonoi et al., 2022b).

The purpose of the study described in this protocol is to confirm the divergence between HbA1c and the rate of glycemic reduction between GA and 1,5-AG in patients with T2D after treatment with 1,000 mg of imeglimin twice daily for 6 months. In addition, we aim to prospectively examine the effects on erythrocytes, the presumed cause of this divergence.

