## 2 Methods/design

### 2.1 Design

The INFINITY study (Comparative evaluation of clinical glycemic control markers treated with ImeglimiN and its eFfect on erythrocytes IN patIents with TYpe 2 diabetes mellitus) is a single-center, single-arm, open-label, prospective study. In clinical practice, the hypoglycemic effect of imeglimin in patients with T2D may differ when measured by HbA1c and GA levels. This study will be conducted in a single-arm, exploratory study (Table 1) because the prolonging of erythrocyte lifespan is postulated as the cause of this divergence. This study will compare HbA1c with the rate of glycemic reduction over time for GA or 1.5-AG to assess whether HbA1c is an appropriate measure. Continuous blood glucose variability measured using flash glucose monitoring (FGM) will also be examined related to changes in these indices to ensure reliability. In addition, because the effect of imeglimin on erythrocyte lifespan is a possible cause of HbA1c deviation, hemoglobin concentration, erythrocyte lifespan, and erythrocyte deformability will also be examined as effects on erythrocytes. Furthermore, if imeglimin ameliorates erythrocyte deformability, it is expected to have the potential to improve peripheral arterial occlusive disease, so an index of arteriosclerosis will also be measured.

**TABLE 1 T1:** Overview of visits and tests schedule.

Item	At informed consent	Pre-observation (months)		Observation period (months)							Follow-up period (months)			At discontinuation		
		−2	−1	0	1	2	3	4	5	6	7	8	9	
Allowable ranges of visits (±weeks)		±2	±2	±2	±2	±2	±2	±2	±2	±2	±2	±2	±2			
Informed consent	X															
Demography	X															
Study drug adherence					X	X	X	X	X	X				X		
Height, body weight				X	X	X	X	X	X	X	X	X	X	X		
Blood pressure, pulse rate				X	X	X	X	X	X	X	X	X	X	X		
Blood tests		X	X	X	X	X	X	X	X	X	X	X	X	X		
Urinalysis				X	X	X	X	X	X	X	X	X	X	X		
Erythrocyte lifespan		X	X	X	X	X	X	X	X	X	X	X	X	X		
Erythrocyte deformability			X	X	X	X	X	X	X	X	X	X	X	X		
Arteriosclerosis/inflammation test				X						X			X	X		
FGM test		X	X	X	X	X	X									
Adverse events		X	X	X	X	X	X	X	X	X	X	X	X	X		

Abbreviations: FGM, flash glucose monitoring.

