### 2.6 Sample size calculation

The target sample size was set to 30.

No data on the effect of imeglimin on erythrocyte lifespan are available; however, in-house data from a Japanese phase 3 study conducted in 27 patients at our clinic showed that imeglimin significantly reduced hemoglobin levels in pre- and post-administration comparisons. Therefore, the sample size was determined based on these data. The mean hemoglobin levels before and 1 year after imeglimin administration were 15.2 and 14.5 g/dL, respectively, with a change of −0.7 g/dL. The standard deviation of the change was 0.8 g/dL; however, in this study, we estimated 1.0 g/dL to account for the study variability. Therefore, the required sample size is 24 when the significance level *α* = 0.05 (two-sided) and the power (1-β) is 90%. Considering dropouts, the target sample size was set to 30. To ensure that enough participants enroll to achieve the target sample size, we have screened potential participants based on inclusion and exclusion criteria, and patients are referred to the study if applicable.

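### The only sized outcome, a hemoglobin change, enters neither condition for the planned conclusion about HbA1c, which rests on unsized, unranked secondary comparisons and on two differing rules

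*Protocol article*

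**What the plan says.** - **Purpose (Introduction).** "The purpose of the study described in this protocol is to confirm the divergence between HbA1c and the rate of glycemic reduction between GA"; the sentence also names 1,5-AG. A second aim follows: "we aim to prospectively examine the effects on erythrocytes, the presumed cause of this divergence".
- **Postulated mechanism (2.1 Design).** "the prolonging of erythrocyte lifespan is postulated as the cause of this divergence". The same section calls the study single-arm and exploratory.
- **Primary outcome (2.3.1).** "Change in hemoglobin concentration between baseline (month 0) and 6 months after treatment with imeglimin".
- **Sample size (2.6).** No lifespan data existed. In-house data from 27 patients showed that "imeglimin significantly reduced hemoglobin levels in pre- and post-administration comparisons": 15.2 to 14.5 g/dL at 1 year. The result is 24 evaluable patients, raised to 30 for dropouts.
- **Secondary outcomes (2.3.2).** Lifespan is item 1, calculated as "Erythrocyte lifespan (days) = K × hemoglobin (g/mL)/endogenous CO (ppm"), with K = 1380. Divergence is covered by item 5 (percent reduction, compared between indices at each time point) and item 6 (the GA/HbA1c and 1,5-AG/HbA1c ratios). None of these is sized or ranked.
- **Conclusion rules.** In the Abstract, if the rates diverge and lifespan is prolonged, "GA and 1,5-AG, rather than HbA1c, will be considered appropriate measures of the hypoglycemic effect" in early treatment. In the Discussion, longer lifespan is the only stated condition for calling HbA1c inappropriate in early treatment.

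**The concern.** The sample size buys certainty about a variable on which the planned conclusion does not depend. The primary test can be significant and leave open whether HbA1c is a sound index for this drug. It can also be non-significant while the divergence is real.

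The questions that matter clinically are left to many secondary comparisons at the same 0.05 level. No visit or index is put first, and two different rules state what would count as an answer. A reader of the eventual report could not tell which result had been meant to decide the matter.

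**Working it through.** **1. The plan's own figure.** Inputs from section 2.6: change 0.7 g/dL, SD 1.0 g/dL, two-sided alpha 0.05, power 90%. Section 2.8 gives the one-sample t-test.
- Standardised effect d = 0.7/1.0 = 0.7.
- Normal approximation: (1.960 + 1.282)²/0.7² = 21.4. Adding the small-sample term 1.960²/2 = 1.92 gives 23.4, so 24.
- Noncentral t: power 0.894 at n = 23 and 0.907 at n = 24.
- Dropouts: 24/(1 − 0.20) = 30. The 20% is implied, not stated.

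The figure reproduces. The arithmetic is sound; the question is what it was applied to.

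**2. Does hemoglobin enter the conclusion?**

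| Place | Condition for the conclusion | Hemoglobin in it? |
|---|---|---|
| Abstract | divergence and longer lifespan | no |
| Discussion | longer lifespan | no |

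**3. What a hemoglobin fall does to calculated lifespan.** Lifespan = 1380 × Hb (g/mL)/CO (ppm).
- With CO unchanged, the ratio after to before is 14.5/15.2 = 0.954, a fall of 4.6%.
- Illustration: a 120-day lifespan at 0.152 g/mL implies CO = 1380 × 0.152/120 = 1.748 ppm. At 0.145 g/mL and the same CO, lifespan = 1380 × 0.145/1.748 = 114.5 days.
- To hold lifespan constant, CO must fall by 4.6%.
- To show a 10% longer lifespan, CO must fall by 1 − 0.954/1.1 = 13.3%.

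Any evidence for longer lifespan must therefore come from CO, not from the hemoglobin fall.

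**4. How many comparisons carry the divergence question?** HbA1c against GA and against 1,5-AG at six on-treatment visits gives 2 × 6 = 12 percent-change contrasts. The two ratios at six visits against baseline give another 12.

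**5. What the sample can detect on an unsized outcome.** The documents give no effect or SD for divergence or lifespan, so d is an assumption (one-sample t, two-sided 0.05):

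| Assumed d | Power, n = 24 | Power, n = 30 | n for 90% |
|---|---|---|---|
| 0.2 | 16% | 19% | 265 |
| 0.3 | 29% | 36% | 119 |
| 0.4 | 47% | 56% | 68 |
| 0.5 | 65% | 75% | 44 |

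Power of 90% needs d of at least 0.69 at n = 24, or 0.61 at n = 30.

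**6. Why the visit matters.** The Introduction reports that HbA1c and GA also diverge with DPP-4 inhibitors at 2 months and then run together. As an illustration, assume a step change in glucose, HbA1c response 1 − (1 − t/120)², and GA response 1 − 0.5^(t/half-life) with the Introduction's 17 to 23 days.

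| Day | HbA1c | GA |
|---|---|---|
| 30 | 44% | 60–71% |
| 60 | 75% | 84–91% |
| 120 | 100% | 97–99% |

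On this model lag alone separates the markers early and has gone by month 6. Both conclusion rules nevertheless speak of early treatment.

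**The case against.** The strongest defence has four parts.

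- **The choice is explained and serves an aim.** Section 2.6 says that no lifespan data existed, and hemoglobin is a named erythrocyte effect in section 2.1 and the Discussion. Sizing an exploratory study on the one erythrocyte variable with data is defensible. This stands, and it is a reason to keep hemoglobin as primary. It does not link a hemoglobin change to divergence or lifespan, and the Introduction's aim to confirm is stronger than exploratory.
- **The protocol never says that hemoglobin carries the HbA1c conclusion.** Correct. A reader might infer that it does from its primary status, but the Abstract and Discussion rest the conclusion on secondary outcomes. The weakness is that those outcomes are unsized and unranked.
- **Lag is recognised.** A reader might infer that the early-treatment conclusion would follow from ordinary marker lag. It would not: both rules also require longer lifespan. The Introduction distinguishes imeglimin by the magnitude and duration of divergence, section 2.1 sets 6 months as the shortest adequate period, and glucose monitoring is added. What remains is narrower: at early visits lag can satisfy the divergence half of the Abstract's rule by itself.
- **Ranking belongs in the analysis plan.** Partly so; section 2.8 defers detail to a plan confirmed before database lock. The two differing conclusion rules, and a primary outcome outside both, are in the protocol itself.

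**Conclusion.** The purpose and the primary outcome do not match, and the conclusion of interest rests on outcomes for which the trial was not sized. This should be corrected; it does not invalidate the study or its sample size calculation.

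The 4.6% reduction in calculated lifespan assumes unchanged CO. It would be too strong to say that a hemoglobin fall contradicts the hypothesis: CO is measured and may fall too, and the test is two-sided on a change. The fall only fails to support longer lifespan.

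Nor do the documents support saying that the question could be re-targeted without more patients. With 24 evaluable patients, power is 90% at 0.69 SD but 65% at 0.5 SD and 47% at 0.4 SD, and nothing in the protocol shows where divergence or lifespan would lie.

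**What to change.** 1. Keep hemoglobin as the registered primary outcome. Limit its claim to an effect on erythrocytes, and state that a fall alone does not support longer lifespan. Replacing the primary during an open-label, single-center study with monthly blood tests would invite doubt that the change was made without knowledge of accruing results.
2. Before month-6 data are analysed, name the month-6 paired difference in percent change from baseline between HbA1c and GA, already within item 5, as the first-ranked key secondary outcome. Name the month-6 lifespan change as the single mechanism test.
3. Reconcile the Abstract and the Discussion so that calling HbA1c an inappropriate measure needs both the month-6 divergence and a lifespan increase. The protocol gives no conversion of GA to a glucose scale, so a difference in percent change alone should not be read as a falsely high HbA1c.
4. Label other visits and indices exploratory.
5. State the precision: 90% power at about 0.69 SD and 65% at 0.5 SD with 24 evaluable patients, with no SD available for divergence or lifespan.

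HbA1c, GA and lifespan are already scheduled at month 6, so patients, visits and assays do not change. The cost is a dated amendment to the protocol and registry entry after enrollment began on 14 February 2023, matching wording in the analysis plan, and a more cautious conclusion.
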